# Culturally adapted psychosocial interventions (CaPSI) for early psychosis in a low-resource setting: study protocol for a large multi-center RCT

**DOI:** 10.1186/s12888-023-04904-8

**Published:** 2023-06-16

**Keywords:** Early psychosis, Psychosocial interventions, Randomized control trial, Pakistan

## Abstract

**Background:**

Psychosis treatment guidelines recommend cognitive behaviour therapy (CBT) and family intervention (FI), for all patients with first episode psychosis (FEP), though guidance borrows heavily from literature in adults from high income countries. To our knowledge, there are few randomized controlled trials (RCTs) examining the comparative effect of these commonly endorsed psychosocial interventions in individuals with early psychosis from high-income countries and no such trials from low and middle-income countries (LMICs). The present study aims to confirm the clinical-efficacy and cost-effectiveness of delivering culturally adapted CBT (CaCBT) and culturally adapted FI (CulFI) to individuals with FEP in Pakistan.

**Method:**

A multi-centre, three-arm RCT of CaCBT, CulFI, and treatment as usual (TAU) for individuals with FEP (*n* = 390), recruited from major centres across Pakistan. Reducing overall symptoms of FEP will be the primary outcome. Additional aims will include improving patient and carer outcomes and estimating the economic impact of delivering culturally appropriate psychosocial interventions in low-resource settings. This trial will assess the clinical-efficacy and cost-effectiveness of CaCBT and CulFI compared with TAU in improving patient (positive and negative symptoms of psychosis, general psychopathology, depressive symptoms, quality of life, cognition, general functioning, and insight) and carer related outcomes (carer experience, wellbeing, illness attitudes and symptoms of depression and anxiety).

**Conclusions:**

A successful trial may inform the rapid scale up of these interventions not only in Pakistan but other low-resource settings, to improve clinical outcomes, social and occupational functioning, and quality of life in South Asian and other minority groups with FEP.

**Trial registration:**

NCT05814913.

**Supplementary Information:**

The online version contains supplementary material available at 10.1186/s12888-023-04904-8.

## Background

Psychosis is one of the 20 leading causes of disability worldwide, affecting 29 million people [1]. A large burden of disease is attributed to people in low and middle-income countries (LMICs) [2]. First Episode Psychosis (FEP) occurs at a young age and is a critical period influencing the long-term course of the disorder. Early psychosis is characterized by repeated relapses, with up to 80% relapsing within 5 years of an initial episode [3]. Relapse causes distress as well as disruption of social and occupational functioning. Relapse following FEP affects long-term psychosocial development at pivotal developmental stages. During early psychosis, pharmacological, social and cognitive interventions can profoundly impact long-term functional outcomes [4]. Antipsychotic medication is effective in reducing risk of relapse [3], however, a significant proportion of patients continue to experience distressing symptoms despite adherence to medication [4].

### Psychosocial interventions for psychosis

Although psychosis treatment guidelines [5–7] endorse psychosocial interventions, namely cognitive behavior therapy (CBT) and family intervention (FI), for all patients with FEP, there are few clinical efficacy trials examining the comparative effects of these interventions in FEP from high-income countries and no such trials to our knowledge from LMICs. The last two decades have seen advances in the development of effective non-pharmacological treatments for psychosis including CBT and FI. A 2021 meta-analysis identified FI and CBT among the most efficacious psychosocial interventions to prevent psychosis relapse in schizophrenia [8]. Meta-analyses have demonstrated that CBT is effective in improving positive and negative symptoms [9], adherence to medication, coping strategies, insight, quality of life and functioning in psychosis [10, 11]. Few studies have shown CBT alone to be more effective than routine care in patients with FEP [12], but use of CBT as an adjunct to pharmacotherapy has been endorsed internationally [5, 13]. Family support is particularly important for those experiencing FEP as illness onset typically occurs when patients are living with caregivers [14]. FEP can be a challenging time as relatives and carers struggle to come to terms with the illness [15]. In LMICs, the responsibility on family members to provide care is further compounded by the lack of trained mental health workers, insufficient resources, and inadequate infrastructure to support mental health services. Families and carers of individuals with psychosis report significant distress, lower quality of life and increased anxiety and depression [16]. Family interventions for psychosis are recommended internationally and have been shown to significantly reduce relapse and readmission rates [17], improve medication adherence [18], enhance functioning [19] and improve family environment [20]. There is evidence for the positive contribution of families towards the wellbeing of people with psychosis, especially when family members are actively supported by psychoeducation, a core component of FI [18, 21]. However, there is limited evidence from LMICs that supports the clinical efficacy and cost-effectiveness of delivering psychosocial interventions in FEP [22, 23].

CBT and FI, like many other modern therapies, were first developed in the West, and as such, largely represent Western cultural values [24]. Social, religious, and cultural factors are known to influence the perception of mental illness, in turn impacting health-related behaviour and engagement with services. The need to culturally adapt these interventions before applying them in non-Western LMICs is clear. Our team has led the first pilot randomized controlled trials (RCTs) of culturally adapted CBT (CaCBT) and culturally adapted FI (CulFI) added to treatment as usual (TAU) for patients with schizophrenia in Pakistan [25, 26]. Building on the preliminary efficacy demonstrated by these pilot RCTs, we propose a three-arm RCT comparing a CBT-focused vs. family-focused intervention vs. TAU for people with psychosis, in a LMIC setting, with the ultimate intent of informing scalable evidence-based care.

### Study objectives

To determine the clinical efficacy of CaCBT and CulFI compared to TAU on reducing overall symptoms of psychosis in patients with FEP in Pakistan.To determine the efficacy of CaCBT and CulFI compared to TAU on positive and negative symptoms of psychosis, general psychopathology, depressive symptoms, quality of life, general functioning, and insight in patients with FEP in Pakistan.To determine the efficacy of CaCBT and CulFI compared to TAU on improving carer experience, carer wellbeing, carer illness attitudes and symptoms of depression and anxiety in family and carers of patients with FEP in Pakistan.To determine the comparative effect of CaCBT and CulFI in improving patient and carer-related outcomes in individuals with FEP in Pakistan.To estimate the cost-effectiveness of delivering culturally appropriate psychosocial interventions in low-resource settings.To explore delivery and reach of each intervention, tolerability of intervention components, acceptability of interventions, understanding mechanism of change and developing an understanding of barriers and facilitators to future adoption using process evaluation.

## Methods/design

### Study design and setting

This is an assessor-masked, three-arm RCT design (trial registration: NCT05814913). Participants (*N* = 390) will include adults with FEP, and will be recruited from ten major recruitment centres (i.e., Karachi, Lahore, Rawalpindi, Hyderabad, Qambar Shahdakot, Shaheed Benazirabad, Sukkur, Peshawar, Quetta and Multan) (*n* = 390, 130 per condition; please see Fig. 1). By recruiting participants from across the country, we are confident that the sample will be representative of Pakistani patients with psychosis.

**Fig. 1 Fig1:**
[figure not shown]
Study Schematic

### Participants

Participants will be included in the study according to the eligibility criteria (Additional file 1: Appendix 1).

### Study interventions

#### Culturally Adapted Cognitive Behaviour Therapy (CaCBT) for psychosis

Participants in the CaCBT group will include adults with FEP who receive 12 individual sessions from a trained Masters level research psychologist over 12-weeks. The number of sessions has been informed by our pilot work [26], where we demonstrated strong recruitment and retention rates, as well as promising effects on improvement of psychosis symptoms. At least 45 min of therapy is offered once a week during the three-month period. Failure to engage will be defined as attendance of less than six therapy sessions (< 50%). Participants will continue TAU alongside the intervention. The CaCBT intervention is based on the intervention manual developed by David Kingdon and Douglas Turkington [27], and culturally adapted by our group. Adaptation focuses on delivery and engagement rather than CBT content. The use of culturally appropriate idioms, drawing on religious teaching, local stories and images has been effective in explaining symptoms and causes of disorders. Patients and their carers in Pakistan use a bio-psycho-spiritual-social model of illness. They seek help from various sources, including faith healers. Therapists, therefore, adjust therapy accordingly. CaCBT aims to take a collaborative approach to gaining an understanding of the symptoms experienced, working towards reducing distress and disability. There are distinct stages, including engagement, the examination of antecedents of the emerging psychotic disorder, the development of normalizing rationale, the treatment of co-morbid anxiety or depression, and collaboratively constructing a case formulation. CaCBT uses specific techniques for positive symptoms of psychosis thereafter. For addressing auditory hallucinations, beliefs about the origin and nature of the experiences(s) are explored using collaborative critical analysis. Strategies such as voice diaries, reattributing the cause of the voices, and development of coping strategies are also employed. Guided discovery and graded homework tasks are used to elucidate delusions. Focusing on specific themes, clarification of neologisms, and thought linkage are some of the techniques used to improve thought disorder. After work on positive symptoms, negative symptoms are targeted using activity scheduling and records of mastery and pleasure in a diary.

#### Culturally adapted Family Intervention (CulFI) for psychosis

Participants in the CulFI group will include adults with FEP and their carers, who will receive 10 sessions of 40–60 min, delivered weekly for the first 8 weeks and fortnightly for the remaining 4 weeks. Sessions are delivered to both patients and their carers, though patient participation in sessions is not necessary. CulFI consists of two integrated manuals, *“Schizophrenia: The Indian scene*” [28] and *“Families of schizophrenic patients: Cognitive behavioural intervention”* [29]. CulFI comprises: family psychoeducation; cognitive-behavioural skills training for stress-management, coping and problem solving; crisis intervention and suicide risk management; relapse prevention; and education and support regarding the family environment, including communication training. The components are designed to facilitate an understanding about psychosis, the emotional impact of the illness on family relationships, to promote more adaptive coping strategies and minimize relapse risk. In our pilot study [25] we demonstrated strong recruitment, retention, and large effect sizes on carer well-being and support. Adaptations to the intervention, akin to those outlined above for CaCBT, followed a rigorous cultural adaptation framework based on our prior work in Pakistan [24, 26, 30].

### Treatment-as-usual (control condition)

There is little if any provision for psychosocial interventions for patients with FEP in Pakistan [31]. Therefore, TAU is essentially the prescription of antipsychotic medication and follow-up appointments with the responsible physician. The medication history of each patient participant will be recorded at visit one. Changes to the participants’ TAU during the study period are permissible, however, responsible physicians will be encouraged to maintain stable TAU and medication will be recorded at each study visit. There is no TAU provided to carers, however, as partners to care they routinely attend follow-up appointments with patients.

### Outcome measures

Primary outcomes will be reduction in symptom severity in FEP as measured by PANSS [32] total score post intervention (three months), six months and twelve months post intervention. All secondary measures including patient and carer outcomes are listed in Additional file 1: Appendix 2.

### Study procedures

Participants will be recruited from ten major centres each with multiple outpatient psychiatric units that provide mental health care to a combined population of over 40 million people. Clinicians will identify potential participants and offer them information about the study. Those who agree will be contacted by the research team, pre-screened, and provided detailed information about the study including procedures protecting privacy and confidentiality. Participants who consent to participate will then undergo a screening assessment based on the eligibility criteria (Additional file 1: Appendix 1), followed by the baseline assessment. The trial manager will confirm eligibility and assign a participant ID number.

### Randomization and masking

Participants (i.e., patients) will be randomised using a secure web-based randomization system. Participants will be allocated to trial groups using permuted block with variable block sizes stratified by site and sex. We have not included additional stratification variables as per best practice in RCTs [33]. We will assess other potential prognostic characteristics (age, duration of illness, gender, sex) in our a priori subgroup analyses. Therapists will contact the participant within 1 week of randomization to inform them about treatment allocation. The time and date of sessions will be set based on the participant’s preference. Participants randomized to the CaCBT group are patients who will receive 12 individual sessions from a trained Masters level research psychologist over 12-weeks. Each session will last for 60 min. Participants in the CulFI group consist of patients and their carers who will receive 10 sessions of 40–60 min, delivered weekly for the first 8 weeks and fortnightly for the remaining 4 weeks. All sessions will be delivered by trained therapists who will receive two months training from senior therapists before starting intervention. The third group will receive TAU. Assessments will be carried out at baseline, months 3, 6, and 12. These scales will be administered in-person and/or via secure videoconference software by trained, blinded research analysts (RAs). This is an assessor masked RCT and due to the nature of the interventions it will be impossible to mask clinicians in participating centres or the participants themselves allocated to the interventions. Participants will be asked before assessments not to reveal any information about treatment to assessors. To avoid unmasking, outcome assessors will be located separately from treatment providers, and we will assign new outcome assessors in cases of unintentional unmasking. Statistical analysis will be partially masked (using treatment group but not what each group is).

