### Sample size

With the proposed total sample size of 390 (130 per condition), we have sufficient power (80%) to detect a small to medium treatment effect (Cohen’s D = 0.39) of either CaCBT or CulFI over TAU on PANSS total score at post-treatment (3-month). The selection of effect size has been informed by a meta-analysis of culturally adapted psychosocial interventions [34] and effect sizes generated from meta-analysis of CBT for psychosis [35]. Cohen’s D of 0.39 is also equivalent to a clinically meaningful reduction in PANSS of 6.70 points. The standard deviation, informed by our pilot work, was taken as 17.18 [26]. For sex or gender-based subgroup analysis, the minimum detectable effect sizes to attain sufficient power increase to 0.48 and 0.67 for men and women respectively. Our exploratory analysis will compare the effect of CulFI with CaCBT in improving patient and carer related outcomes. Although this exploratory outcome is not adequately powered for a non-inferiority analysis, it will inform sample size for future comparative clinical trials. The power calculation has considered 20% attrition at post treatment and was based on an end-point analysis. Longitudinal analysis will be more powerful with reduction in measurement error due to repeated measures.

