### Statistical analysis

Descriptive analysis will first be conducted for the baseline data to inspect group differences across the three conditions. Patterns of missing outcome data will be examined as a function of recorded baseline characteristics and patterns of compliance with the protocol. For the primary and secondary aims, linear mixed-effects models will be the main analytic strategy and will be conducted under an intention-to-treat framework. A multiple imputation approach will be employed as the missing data method to account for potential bias caused by attrition. Two types of analysis will be conducted to evaluate the treatment effects of CaCBT and CulFI compared to TAU. An endpoint analysis will focus on the pre-post difference at 3 months and a longitudinal analysis will inspect change overtime (baseline, 3 months, and 6 and 12-months post intervention) regarding long-term effect and sustainability. Treatment assignment and its interaction with time will serve as the primary predictors with site, key demographics and baseline outcome measure being controlled as covariates. For moderation analysis concerning biological sex and gender, we will include interaction between treatment assignment and sex and gender in the endpoint analysis and add time to form three-way interaction in the longitudinal analysis. Moderation effects of sex and gender will be assessed in separate models so their effects can be estimated independently. Similar approaches will be applied for secondary outcomes and generalized linear mixed effects models will be in place for binary outcomes. For the exploratory aim to compare effect of CaCBT and CulFI in improving patient and carer related outcomes, we will conduct noninferiority tests to evaluate if the difference between CaCBT and CulFI is within the noninferiority margin for each individual outcome. The noninferiority margins will be determined carefully following well-accepted guidelines [36] and clinical knowledge.

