#### Subgroup analysis

Subgroup analysis will be carried out with respect to age, gender, duration of illness, and sex by adding a treatment with covariate interaction into the primary analysis model. Gender and sex will be included in separate models to evaluate independent impact.

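### The main model names only one of the two randomisation strata, and duration of illness, listed as potentially prognostic, enters only through subgroup interactions: a free, minor improvement

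*Protocol article*

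**What the plan says.** Three sections of the protocol article bear on this.

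- **Randomization and masking.** Allocation is done "using permuted block with variable block sizes stratified by site and sex". The section says that no further strata are used and cites best practice for that choice. It then adds: "We will assess other potential prognostic characteristics (age, duration of illness, gender, sex) in our a priori subgroup analyses".
- **Statistical analysis.** The main linear mixed models have treatment and its interaction with time as primary predictors, "with site, key demographics and baseline outcome measure being controlled as covariates". The key demographics are not itemised. Sex and gender are named in this section only for the moderation analyses.
- **Subgroup analysis.** Age, gender, duration of illness and sex are examined "by adding a treatment with covariate interaction into the primary analysis model", with gender and sex in separate models.

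**The concern.** When randomisation is stratified, the analysis should normally carry the strata. Stratification makes the arms alike on the factor, but a model that omits the factor leaves its variation in the residual. The standard error then takes no account of the balance achieved and is too large to the extent that the factor predicts outcome. Here the model names site and leaves sex, the other stratum, to be inferred.

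Duration of illness raises a related point. The plan itself calls it potentially prognostic, yet its only stated role is as a subgroup variable. A treatment-by-duration interaction asks whether the effect of CaCBT or CulFI differs between patients with short and long illness. Such a model would contain a main effect of duration, but its result is a subgroup result. The overall comparison with TAU still comes from a model that, as described, does not include duration.

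At stake is some precision in a trial planned at 80% power, and clarity about which covariates were fixed in advance.

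**Working it through.** **1. The plan's own figure.** Inputs from the Sample size section: difference 6.70 PANSS points, SD 17.18, power 80%, attrition 20%, 130 per arm. Alpha is not stated; I assume two-sided 0.05 per comparison.

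- Standardised effect: 6.70 / 17.18 = 0.39.
- Evaluable per arm: 2 × (1.960 + 0.842)² × (17.18 / 6.70)², rounded up = 104.
- Randomised per arm: 104 / 0.80 = 130, as stated.
- Power at 104 per arm: SE = 17.18 × √(2/104) = 2.38; 6.70 / 2.38 = 2.81; Φ(2.81 − 1.96) = 0.803.

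The figure reproduces. The calculation is unadjusted and takes no credit for stratification or covariates.

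**2. Precision gained by adding one factor as a main effect.** Let ρ be the correlation of the factor with 3-month PANSS beyond the covariates already in the model. The article gives no value, so I show an assumed range. Residual variance falls by ρ², and the SD becomes 17.18 × √(1 − ρ²). I apply this to the planning SD of 17.18.

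| ρ (assumed) | Variance removed | SD | Power at 104 per arm |
|---|---|---|---|
| 0 | 0% | 17.18 | 0.803 |
| 0.1 | 1% | 17.09 | 0.807 |
| 0.2 | 4% | 16.83 | 0.819 |
| 0.3 | 9% | 16.39 | 0.838 |

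**3. If sex were left out of the model.** The standard error would be too large by a factor of 1 / √(1 − ρ²): 1.005 at ρ = 0.1 and 1.048 at ρ = 0.3. The error is in the conservative direction.

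**4. Chance imbalance in duration of illness.** With 104 evaluable per arm, the standard error of a standardised difference between two arms is √(2/104) = 0.139. An imbalance of 1.96 standard errors is 1.96 × 0.139 = 0.27 SD of the factor. If the factor is not adjusted for, the contrast in that one realised sample moves by 0.27 × ρ × 17.18, which is about 0.5, 0.9 and 1.4 PANSS points for ρ = 0.1, 0.2 and 0.3, against a target of 6.70. Over repeated randomisations the shift averages zero, and the unadjusted standard error already allows for it.

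**5. What the interactions can show.** The minimum detectable effects of 0.48 (men) and 0.67 (women) in the Sample size section correspond to about 69 men and 36 women evaluable per arm, 105 in all, which fits the 104 above. The standard error of a difference between the two sex-specific effects is √(2/69.1 + 2/36.0) = 0.291. The detectable difference at 80% power is 2.80 × 0.291 = 0.81 SD. These tests address effect modification, and only for large differences. They add no precision to the overall contrast.

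**The case against.** The best defence is that the adjustment is largely in place. The main model already includes site, the baseline outcome and key demographics. Age and sex are ordinary demographics and plausibly belong to that set, and baseline PANSS probably carries much of the prognostic information. A journal article may leave the covariate list to a full protocol or SAP that is not shown. Using sex both as a stratum and as a subgroup factor is legitimate. All of this stands, and it keeps the point minor.

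Three stronger readings are tempting, and the article supports none of them.

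- A reader might infer that subgroup tests are offered as the remedy for imbalance in unstratified factors. The article does not say so. Its reason for using no further strata is best practice, and the subgroup sentence follows separately without mentioning imbalance or adjustment. Limiting the strata to two is sound.
- A reader might infer that sex is certainly absent from the main model. The text leaves it unnamed; it does not exclude it.
- A reader might infer that the primary estimate is biased. Randomisation protects it: chance imbalance does not bias the estimator on average.

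The defence does not cover two things. Duration of illness is a clinical variable, so a set of demographics does not naturally include it. And the sentence that lists sex among the other factors is inaccurate as written.

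**Conclusion.** The point holds as a free improvement of minor severity. The covariate description names one stratum and leaves the other to inference, and a factor that the plan calls potentially prognostic has no main-effect role in the primary comparison. Calling sex one of the other characteristics is a wording slip and does not obscure the randomisation scheme.

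No stated figure changes; N stays at 390. For a residual correlation of 0.1 to 0.3, main-effect adjustment for one factor removes 1% to 9% of residual variance and raises power by at most 0.035 (0.803 to 0.838). Omitting sex would overstate the standard error by at most about 5% over the same range, with no increase in false positives. These sizes rest on the assumed correlations, on two-sided alpha of 0.05 per comparison, and on 104 evaluable patients per arm.

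**What to change.** - **Statistical analysis:** name sex together with site as a fixed covariate in the primary and secondary models, since both are randomisation strata. Add baseline duration of illness as a prespecified main effect, and age too if it is not already among the key demographics.
- **Subgroup analysis:** keep the treatment-by-covariate interactions for effect modification only.
- **Randomization and masking:** remove sex from the other prognostic characteristics, or say that it is a stratum that will also be examined as a subgroup factor.

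The cost is a change of wording and at most three model degrees of freedom (sex, age and duration, the last two as continuous terms) in about 3 × 104 = 312 evaluable patients. The planned subgroup analyses already require all of these variables, so no new data are needed.
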